### Procedures

A nurse in the paediatric oncology unit will screen for eligibility for all patients who are admitted to receive their first intravenous chemotherapy during pre-chemotherapy assessment. If children meet the inclusion criteria, the nurse will refer them and their accompanying parents to the RA who will give them an information sheet, explain the trial and show the IVR equipment. If they agree to participate, an informed consent will be obtained from the accompanying parents. The RA will then acquire socio-demographics and clinical characteristics of the patients from medical record. According to the subject allocation, children in the control group will receive standard care, while the intervention group will additionally receive the IVR intervention.

Four hours prior to (T0), immediate before first course (T1), and second course of chemotherapy begins (T3), a set of data (i.e. anxiety, HR & BP and anticipatory CINV) will be collected from the patients. Immediate after the first (T2) and second course of chemotherapy (T4), the anxiety, HR & BP and acute CINV will be collected. In the intervention group, the timing and duration of IVR use and modules selected will also be recorded. The SPIRIT schedule of the trial is shown in Fig 1.

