## Introduction

Chemotherapy treatment can provoke anxiety in many patients [1]. In particular, patients usually exhibit a heightened level of anxiety when receiving their first chemotherapy [2]. An observational study found that 89% of chemotherapy-naïve patients experienced pre-chemotherapy anxiety. Paediatric cancer patients exhibiting elevated anxiety level early in the therapy are four times more prone to have elevated anxiety after the treatment [1]. Moreover, pre-chemotherapy anxiety, as well as anxiety experienced after chemotherapy start, expose patients to a higher risk of chemotherapy-induced nausea and vomiting (CINV) [3, 4].

CINV remains the most frequent and unpleasant side effect in paediatric patients receiving chemotherapy [5]. Acute CINV refers to symptoms that occur within 24 hours of chemotherapy administration [5]. Anticipatory CINV may develop without proper initial management. Anticipatory CINV is a conditioned response that occurs prior to a subsequent initiation of chemotherapy upon being re-exposed to the stimuli that signal the chemotherapy infusion [5]. A meta-analysis of 35 studies reveal that 30% of adult and paediatric patients reported anticipatory CINV [6]. One known factor associated with CINV development among paediatric patients is emetogenicity of chemotherapy [7]. However, pharmacological treatments for CINV prevention are still suboptimal [5].

Poorly managed anxiety and CINV lead to physical consequences, such as dehydration and electrolyte imbalance, and hinder the patients’ ability to cope with subsequent chemotherapy. This phenomenon may lead to the delay or discontinuation of treatment and affect treatment and survival outcomes [7]. CINV is the most aversive condition that greatly distresses patients and parents, thereby reducing their satisfaction to care [7].

Effective management of anxiety and CINV is critical for children receiving their first chemotherapy; in particular, anticipatory and acute CINV increase with time [6]. International guidelines recommend optimal psychological interventions be offered to children for anticipatory CINV [8]. Therefore, psychological interventions are needed to help paediatric cancer patients to cope with anxiety and CINV on their first chemotherapy.

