### Intervention: IVR

Participants receive IVR for three separate sessions in the first and second course of chemotherapy: (1) 4 hours prior to the chemotherapy commenced, (2) 5 minutes before and during the first chemotherapy and (3) 5 minutes before and during the second chemotherapy. Considering additional sessions may result in missing data despite enhancing the intervention effect, therefore, three sessions of IVR appears feasible [21].

The first IVR session is used to establish a relaxation and playful response to participants before the chemotherapy commenced. As patients are usually admitted in the morning to prepare for chemotherapy infusion that is commenced in the afternoon, the first IVR session is held 4 hours before commencement of chemotherapy for practical reason. The second IVR session is used to establish IVR as counter conditioning and distraction intervention during chemotherapy infusion to reduce the anxiety and CINV of patients. The third session aims to determine if IVR has stable effects on reducing anxiety and CINV, and whether or not patients can sustain their interest in IVR.

During the intervention, the patients experience the sense of immersion through a head-mounted device delivering IVR sounds and images by using disposable Google cardboard goggles that can be fitted to both Apple and Samsung smartphones. Latest headsets (Oculus Rift or HTC Vive) may increase contact infection risk and therefore not used in this trial.

Our previous work on IVR among paediatric cancer patients found that three-dimensional cartoon videos, such as Minions or Cut the rope, are preferred by patients aged below 12; however, VR sceneries are not selected by any children. As such, four 3D cartoon modules, which provide a wide range of visual and auditory stimuli and can be freely downloaded, are provided for the patients. These modules are considered as appropriate after consultation with oncologists, nurses in paediatric cancer units and an IT specialist. These videos are also interesting and captures the attention of patients for an extended period of time [15].

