Anxiety: The short form of the Chinese version of the State Anxiety Scale for Children (CSAS-C) will be used to measure the self-reported anxiety levels of the participants in the trial [22]. This measurement uses a three-point Likert scale with 10 items and total scores ranging from 10 to 30, with higher scores indicating higher anxiety levels [22]. The State Anxiety Scale has been used in our previous IVR trial to measure anxiety among children undergoing needle-related procedures, with a Cronbach’s alpha coefficient of 0.89 [15].Heart rate and mean arterial blood pressure: The physiological responses of anxiety will be measured by heart rate and mean arterial blood pressure (HR & BP) using a standard automatic blood pressure monitoring machine (available in the study institution). These indicators are considered to be objective and definitive in assessing physiological responses of anxiety [10, 11].Anticipatory nausea and vomiting: A visual analogue scale (VAS) will be used to assess the severity of nausea and vomiting before the chemotherapy. Children will be asked to indicate their severity of nausea and vomiting on a 0–100 mm horizontal line, with “0” indicating the absence of nausea and vomiting while “100” indicates the most severe form of nausea and vomiting.Acute nausea and vomiting: The MASCC Antiemesis Tool (MAT) will be adopted to assess the chemotherapy-induced nausea and vomiting. The Chinese version has good reliability and validity with a Cronbach’s alpha coefficient of 0.73 [23]. The four items assessing acute CINV will be used in this trial.*Satisfaction*

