**Fig 1 pone.0258514.g001:**
[figure not shown]
SPIRIT schedule of the trial. T0: Pre-test data 4 hours prior to chemotherapy; T1: Immediate before 1^st^ chemotherapy starts; T2: Immediate after 1^st^ chemotherapy; T3: Immediate before 2^nd^ chemotherapy starts; T4: Immediate after 2^nd^ chemotherapy. ^1^IVR: Immersive virtual reality; ^2^CSAS-C: The short form of the Chinese version of the State Anxiety Scale for Children’.

Individual face-to-face semi-structured interviews will be conducted at T4 with patients in the interventional group, their accompanying parents and oncology nurses involved in the chemotherapy administration. Frequency of vomiting will be obtained from medical record (T0-T4). All children will be given the Google cardboard goggles after the completion of trial. The flow diagram of trial design is shown in Fig 2.

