However, several limitations of this trial must be acknowledged. First, only paediatric cancer patients between the ages of 6–12 years will be recruited. Patients under six years of age who are prone to anxiety during chemotherapy will not be included. Therefore, the trial results may not be able to generalise to other age groups. Second, this trial will only be conducted in a single institution so contamination between intervention and control group cannot be ruled out. Nevertheless, the intervention will take place in the patients’ rooms to minimize potential bias. Finally, the trial will only examine the preliminary short-term effects of IVR intervention on anxiety and CINV outcomes (after the second chemotherapy). Therefore, the sustainability of IVR intervention over long periods cannot be determined.

In summary, the proposed IVR intervention will potentially provide insights into the feasibility and acceptability of IVR intervention in managing anxiety, nausea and vomiting among paediatric cancer patients receiving their first chemotherapy. The results will provide a foundation for future studies.

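### Acute CINV is defined over 24 hours, but the acute MAT items are asked as soon as each course ends, so later nausea in both courses and vomiting after the second are not captured.

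*Protocol article*

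**What the plan says.** The Introduction sets the outcome window: "Acute CINV refers to symptoms that occur within 24 hours of chemotherapy administration".

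Measurements assigns the MASCC Antiemesis Tool to this outcome: "The four items assessing acute CINV will be used in this trial". It gives no separate time of administration and no recall period.

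Procedures fixes the timing: "Immediate after the first (T2) and second course of chemotherapy (T4), the anxiety, HR & BP and acute CINV will be collected". The Fig 1 caption agrees ("T2: Immediate after 1^st^ chemotherapy", with T4 defined in the same way for the second course) and lists no time point beyond T0 to T4. The figure itself is not available, but its caption lists the full set of time points.

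The text after the Fig 1 caption adds a second source, for vomiting only: "Frequency of vomiting will be obtained from medical record (T0-T4".

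The limitations in the Discussion confirm that follow-up ends there: "the trial will only examine the preliminary short-term effects of IVR intervention on anxiety and CINV outcomes (after the second chemotherapy".

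**The concern.** At T2 a child can report only what has already happened. If the window is 24 hours and the question is put when administration stops, symptoms in the rest of the window have not yet occurred and no later question picks them up. T3 does not fill the gap, because the nausea and vomiting measure taken then is the anticipatory visual analogue scale before the second course.

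Acute CINV is among the main outcome measures in the Abstract, is part of the second objective, and is a target of IVR sessions 2 and 3. Data analysis plans GEE models and Cohen's d for each outcome. For acute CINV these would rest on the T2 and T4 readings. The Discussion says the trial should help to determine suitable outcome measures for a definitive trial. A shortened measure carrying the full outcome's name would misinform that choice, and no analysis can recover symptoms that were never recorded.

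**Working it through.** The protocol states no figure to reproduce here. The check has two parts.

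**1. Share of the 24-hour window still to come when the MAT items are asked**

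Inputs:
- Window: 24 h (Introduction).
- Assessment: end of administration, T2 and T4 (Procedures, Fig 1 caption).
- Infusion length h: not stated. Intervention: IVR says only that patients are prepared for a "chemotherapy infusion that is commenced in the afternoon". I assume 0.5 to 24 h.

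The Introduction's wording does not say whether the clock starts at the beginning or the end of administration, so both are shown.

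Clock from the start: share missed = 1 − min(h, 24)/24. For example, h = 4 gives 1 − 4/24 = 83.3%.

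| Infusion length (h, assumed) | Window elapsed at T2/T4 | Window missed |
|---|---|---|
| 0.5 | 2.1% | 97.9% |
| 1 | 4.2% | 95.8% |
| 2 | 8.3% | 91.7% |
| 4 | 16.7% | 83.3% |
| 6 | 25.0% | 75.0% |
| 8 | 33.3% | 66.7% |
| 12 | 50.0% | 50.0% |
| 18 | 75.0% | 25.0% |
| 24 | 100.0% | 0.0% |

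More than half is missed whenever h is below 12.

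Clock from the end: almost none of the window has elapsed at T2 or T4, so about 100% is missed whatever h is.

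On the first clock, two children with infusions of 2 h and 8 h would be observed for 8.3% and 33.3% of the same nominal window. Their scores would differ in meaning for that reason alone.

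**2. What any source captures after administration ends**

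| Component | Course 1 | Course 2 |
|---|---|---|
| Nausea | Not captured as acute CINV: MAT asked at T2, record covers vomiting only | Not captured: MAT asked at T4, record covers vomiting only |
| Vomiting | Charted episodes captured, since T2 to T3 lies inside T0-T4; no 0-24 h window stated | Not captured: the record extraction also stops at T4 |

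Three of the four cells are empty. The direction of the error needs no model: whether a symptom occurred, how often, and how severe it was at its worst cannot be greater over part of a window than over the whole. The level of acute CINV is therefore understated, or at best equal. Cohen's d would describe the shortened window; whether it would be larger or smaller than over 24 hours cannot be derived from the protocol.

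**The case against.** The strongest reply is that this is a feasibility study of 20 children. CINV is collected as preliminary data, and testing the data collection procedure is itself an objective. IVR is given as distraction during the infusion, so a reading at the end of the infusion matches the period of exposure. This stands as a reason for measuring something at T2 and T4. It does not justify calling the result acute CINV, which the protocol defines over a longer period.

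Three stronger readings are tempting, and the protocol does not support them.

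- **That most of the window is never observed.** This is too broad. Charted vomiting after the first course lies inside T0-T4. For the MAT items, whether most of the window is missed depends on an infusion length the protocol does not give: on the clock from the start, it fails at 12 h or longer. The length of a course is not stated either.
- **That vomiting is reduced to one pooled T0-T4 count.** The sentence on the medical record may equally mean extraction by time point or interval. What can be said is that no 0-24 h window is stated and that extraction stops at T4.
- **That acute CINV will sit near zero in both arms.** This needs an assumed incidence, infusion length and constant hazard, none of them in the protocol. With a true 24-hour incidence p, the proportion showing a first event by h hours would be 1 − (1 − p)^(h/24). That gives 3% for p = 0.5 and h = 1, but 26% for p = 0.7 and h = 6, and 45% for p = 0.7 and h = 12. The formula also models any event, whereas the outcome is a four-item tool.

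**Conclusion.** The inconsistency is real and rests on stated text, not on detail left out of an article: the outcome is defined over 24 hours and collected when administration ends. As written, nausea after the end of administration is not captured as acute CINV in either course, and vomiting is not captured after the second. These gaps exist for any infusion shorter than 24 h if the clock starts with administration, and for every infusion if it starts at the end.

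Their size depends on the unstated infusion length: about 98% to 0% of the window over an assumed 0.5 to 24 h on the first clock, and about all of it on the second. The observed window would also vary between children with infusion length. The preliminary acute CINV data would understate the outcome as defined, and the effect sizes built on them would not be those of 24-hour acute CINV. No claim is made about how low the observed scores would be.

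**What to change.** Keep T2 and T4 for anxiety, heart rate and blood pressure. Give the four MAT acute items once at 24 hours after each course, with one fixed clock start (beginning or end of administration) written into the protocol and used for every child. The existing research assistant can do this on the ward, or by phone after discharge. Extract charted vomiting over the same 0-24 h window after each course, including the second, and add these time points to Procedures and Fig 1.

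The cost is a schedule amendment and 20 children × 2 courses = 40 short contacts. The research assistant is part-time and some contacts will be missed after discharge, so the number missed should be reported; it is itself useful feasibility information. The interval between courses is not stated, so the site should confirm that the first 24-hour contact falls before the second course. Trial status says data collection was still ongoing at first submission, so the change could have served only children not yet assessed. Data already collected at T2 and T4 should be reported separately.

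If 24-hour contact is not feasible, rename the outcome as nausea and vomiting during chemotherapy administration, report infusion length beside it, and do not present it as acute CINV.

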**Fig 1 pone.0258514.g001:**
[figure not shown]
SPIRIT schedule of the trial. T0: Pre-test data 4 hours prior to chemotherapy; T1: Immediate before 1^st^ chemotherapy starts; T2: Immediate after 1^st^ chemotherapy; T3: Immediate before 2^nd^ chemotherapy starts; T4: Immediate after 2^nd^ chemotherapy. ^1^IVR: Immersive virtual reality; ^2^CSAS-C: The short form of the Chinese version of the State Anxiety Scale for Children’.

Individual face-to-face semi-structured interviews will be conducted at T4 with patients in the interventional group, their accompanying parents and oncology nurses involved in the chemotherapy administration. Frequency of vomiting will be obtained from medical record (T0-T4). All children will be given the Google cardboard goggles after the completion of trial. The flow diagram of trial design is shown in Fig 2.

**Fig 2 pone.0258514.g002:**
[figure not shown]
Flow diagram of trial design. ^a^ blood pressure; ^b^ heart rate; ^c^ chemotherapy-induced nausea and vomiting; ^d^ immersive virtual reality.

### Data analysis

IBM SPSS for Windows (Version 26) will be used. Appropriate descriptive statistics will be used to summarise data such as screening, eligibility, consent and withdrawal rates.

Continuous demographic (e.g. age) and clinical variables (e.g. scores on CSAS-C) will be presented by their means and standard deviations, whereas categorical data (e.g. sex) will be presented in frequencies and percentages. Pearson’s chi-square test (or Fisher’s exact test) and independent t-test (or Mann-Whitney test for highly skewed data) will be used as appropriate for assessing the homogeneity of the baseline characteristics of the two groups. The intention-to-treat principle will be adopted in the outcome evaluation between the two groups [25]. Generalized estimating equations model will be used to compare each of the outcome measures across the time points between the two groups. GEE model can account for intra-correlated repeated measures data and produce unbiased estimates even in the presence of missing data, provided they are missing at completely random. Potential confounders on the outcome variables, including duration of IVR used, will be adjusted in the GEE models to improve the precision of the effect estimates. Cohen’s d values will also be calculated to estimate the effect sizes of the IVR intervention on the outcome variables. All statistical analyses are two-sided and level of significance will be set at 0.05.

All interviews will be transcribed verbatim into written Chinese before conventional content analysis is conducted. Starting with line-by-line coding, statements that are related to (1) the acceptability and feasibility of the intervention and (2) acceptability and feasibility of trial procedures will be coded and categorized. Once the categories have ample data, they will be broken down into sub-categories. The categories and subcategories will be reviewed by two co-investigators to ensure participants’ points of views are accurately reflected. Appropriate strategies will be undertaken to ensure the trustworthiness including credibility, dependability, confirmability, and transferability [27].

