### Sample size calculation

In 2017, about 28 paediatric cancer patients aged between 6 and 12 years were admitted to the study institution for their first chemotherapy. This exploratory trial recruits 20 patients, 20 accompany parents and 10 oncology nurses involved in the administration of chemotherapy. Based on our previous trial on paediatric patients with cancer, this sample size can be realistically recruited within the study period and is adequate for the objectives of the trial [11, 15].

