### Randomisation and blinding

This exploratory trial comprises two groups: an intervention group that receives the IVR intervention and standard care and a control group that receives standard care only. A computer-based stratified randomization is used to randomly assign patients into one group or the other. Strata are constructed on the basis of cancer types, approach commonly adopted in previous studies [6, 11]. Randomization is conducted by an independent statistician.

The nature of an IVR intervention may be impractical for the blinding of participants and interventionists. Nevertheless, the lack of blinding does not necessarily contribute to a source of bias because children are unlikely to change their behaviours even when they are aware of participating in a certain intervention [10, 11].

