The parent and nurse satisfaction levels toward the chemotherapy procedure will be assessed by questionnaires developed by Tyson and colleagues [24]. The original English questionnaire for parents is a 10-item scale rated on a five-point scale ranging from 1 = strongly disagree to 5 = strongly agree. Higher scores indicate higher levels of satisfaction. The satisfaction of the nurses will be examined by eight items, with each being rated on a scale from 1 = strongly disagree to 5 = strongly agree. The first author ([name]) has translated both questionnaires into Chinese using the back-translation method [25, 26]. The translated version was reviewed by a panel of expert professionals for semantic and content equivalence. This scale has been used in previous trial to assess the satisfaction level of parents and health care professionals toward a medical procedure with the reported Cronbach’s alpha 0.90 for both scales [10].*Acceptability of the intervention*
Individual face-to-face semi-structured interviews will be conducted using an interview guide with 10 patients, their accompanying parents and the nurses who administrate chemotherapy to the intervention group. The interviews with the patients aim to explore their experiences, acceptance, satisfaction and any improvements of the IVR intervention. The interviews with parents aim to explore their acceptance and possible improvements in implementing IVR for their child. The interviews with nurses aim to determine the feasibility of integrating IVR intervention into their routine clinical practice and any possible improvements. The RA, who also has considerable experience in qualitative research, will conduct the interviews. Each interview will be audio-taped and conducted in a quiet room provided at the study institution.*Socio-demographic and clinical characteristics*
The following clinical characteristics will be collected from participant’s medical record: age, gender, year of study, medical diagnosis, time since diagnosis, stage of disease, type of cancer treatment received, chemotherapy regimen, types and dosage of antiemetic prescribed and intake. These will be useful in providing baseline information for optimizing design and subject recruitment for the future definitive trial.

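### Baseline p-values and a post-randomisation adjuster are named where the T0 value and the randomisation stratifier would do the work

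*Protocol article*

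**What the plan says.** All references are to the protocol article.

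- **Data analysis, baseline.** Chi-square or Fisher tests and t or Mann-Whitney tests "will be used as appropriate for assessing the homogeneity of the baseline characteristics of the two groups". Nothing says what follows from a significant or a non-significant result.
- **Data analysis, outcomes.** Each outcome is compared between groups over the time points by GEE. Potential confounders are to be adjusted for in order to gain precision, and the one example is the duration of IVR use. On testing: "All statistical analyses are two-sided and level of significance will be set at 0.05". Cohen's d is also to be reported.
- **Randomisation and blinding.** "Strata are constructed on the basis of cancer types". The number and definition of the strata are not given.
- **Procedures.** Anxiety, heart rate, blood pressure and anticipatory CINV are measured at T0. Acute CINV (MAT) is measured only at T2 and T4.
- **Introduction.** "One known factor associated with CINV development among paediatric patients is emetogenicity of chemotherapy".
- **Measurements.** Clinical data taken from the record include "chemotherapy regimen, types and dosage of antiemetic prescribed and intake".
- **Sample size calculation.** "This exploratory trial recruits 20 patients, 20 accompany parents and 10 oncology nurses involved in the administration of chemotherapy".

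**The concern.** There are three linked problems in one paragraph of the analysis plan.

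First, after randomisation any baseline difference is due to chance, so a test of homogeneity tests a null hypothesis that is true by design. In a trial this small it will also label quite large chance differences as homogeneous.

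Second, the one adjuster named cannot do what the sentence asks of it. Under Control: Standard care, controls receive no IVR, so duration is absent (in effect zero) throughout one arm and is a consequence of allocation in the other. With it in the model, the group coefficient no longer compares the arms as randomised. It becomes an extrapolation to an intervention child with no IVR exposure.

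Third, the variables that could add precision are at hand but not named: the T0 measurement and the factor on which randomisation was stratified.

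At stake are the between-group estimates and Cohen's d values, which the article intends as preliminary data for a definitive trial. A chance difference at T0 that goes unaddressed would carry into that planning.

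**Working it through.** **Inputs.** The total of 20 children is from Sample size calculation. That section gives no effect size, SD or power. It rests on the statement that "this sample size can be realistically recruited within the study period and is adequate for the objectives of the trial", so there is no power figure to reproduce. The allocation ratio is not stated. I assume 10:10, because "Individual face-to-face semi-structured interviews will be conducted using an interview guide with 10 patients" and Procedures places the patient interviews in the intervention group. Alpha is two-sided 0.05. The correlation r between T0 and follow-up and the effect d are not in the document and are assumed below.

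**1. What a baseline t-test can show with 10 per arm.**
- Standard error of the difference, in SD units: √(2/10) = 0.447.
- Critical t on 18 df: 2.101. The observed difference must therefore reach 2.101 × 0.447 = 0.94 SD before it is flagged.
- An observed difference of 0.5 SD gives t = 0.5/0.447 = 1.12, p = 0.28, and would be read as homogeneous.
- Power against a 0.5 SD shift (noncentral t, 18 df, noncentrality 1.12): 18.5%, about 19%.
- In the other direction, ten independent baseline tests (number assumed) give 1 − 0.95¹⁰ = 40% chance of at least one p < 0.05 under faultless randomisation.

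**2. The same for a binary factor.** Suppose 10 of the 20 children have a given characteristic and allocation is 10:10 without stratification (both assumed).
- P(split of 7:3 or worse) = 33052/184756 = 17.9%.
- Fisher's exact p for a 7:3 split is 0.18, so the test would not flag it.

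**3. What T0 adjustment is worth.** Take one follow-up time, equal variances at T0 and follow-up, and complete data. In units of the unadjusted variance:
- change from T0: 2(1 − r)
- adjusted for T0: 1 − r²
- ratio, adjusted to change: (1 − r²)/[2(1 − r)] = (1 + r)/2

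| r (assumed) | change | adjusted | ratio | children needed with change, relative to adjusted |
|---|---|---|---|---|
| 0.3 | 1.40 | 0.91 | 0.65 | 1/0.65 = 1.54 |
| 0.5 | 1.00 | 0.75 | 0.75 | 1/0.75 = 1.33 |
| 0.7 | 0.60 | 0.51 | 0.85 | 1/0.85 = 1.18 |

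For scale, with d = 0.8 (assumed) and 10 per arm, the unadjusted comparison at one time point has 39.5% power. The change contrast has about 30%, 40% and 59% at the three correlations. The T0-adjusted contrast has about 40%, 47% and 63%, after allowing for the covariate (17 df, variance inflated by 1 + 1/16).

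The comparison with the change score applies only if T0 is a response in an unconstrained group-by-time model. The article does not say whether it is.

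**The case against.** The strongest counter-argument is that the plan does adjust. Its list of confounders is open, so cancer type and emetogenicity may be on it, and a full covariate list is commonly left to an analysis plan that is not shown. This stands as far as it goes: the absence of a list is not the point. What remains is that the article does state a choice. It commits to baseline tests, and the single covariate it gives is unsuitable.

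A reader might infer that T0 is certainly handled as a response, so that the loss in the table is certain. The text does not settle this. If T0 is already a covariate, that loss is nil.

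A reader might also infer that the plan neglects the main determinant of CINV. The Introduction calls emetogenicity one known factor, not the determinant. It is not recorded as such, but could be derived from the regimen. It may also follow cancer type, in which case the stratification already limits imbalance, and the 17.9% above overstates the risk because it ignores the strata. Nor does that figure support calling such an imbalance likely.

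The benefit of T0 is also uneven. MAT acute CINV has no T0 value. The VAS at T0 may sit near its floor, because the Introduction defines anticipatory CINV as a conditioned response before a later chemotherapy and these children are chemotherapy-naïve.

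Finally, feasibility and acceptability are the main aims, and the article ties no decision to the baseline tests. This limits the harm but does not remove it, since two-sided tests at 0.05 and effect sizes are still planned.

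**Conclusion.** The point holds in a limited form. The baseline significance tests are uninformative: about 19% power against 0.5 SD, assuming 10 per arm. The only adjuster named is post-randomisation and absent in controls. The T0 value and the stratifier are not named, and the role of T0 in the GEE is left open.

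If T0 is a response time point, adjusting for it would multiply the variance of the T0 contrast by 0.65 to 0.85. This rests on assumed r from 0.3 to 0.7, a single follow-up and complete data, and applies mainly to CSAS-C, heart rate and mean arterial pressure.

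The documents do not support saying that the plan makes no baseline adjustment, or that omitting emetogenicity is an error. This is an inexpensive improvement to an exploratory analysis and does not threaten the trial's feasibility aims.

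**What to change.** In Data analysis:

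1. Replace the baseline tests with a descriptive table by arm, without p-values.
2. State how T0 enters the model. For CSAS-C, heart rate, mean arterial pressure and, where it is informative, the VAS, model the post-baseline values with the T0 value as covariate, or use a model that constrains the arms to a common T0 mean. T0 must be taken before the first IVR session to count as baseline; the Fig 1 legend calls it pre-test, and the analysis text should say so.
3. Include cancer type as used in the randomisation, collapsed if strata are sparse.
4. Restrict covariates to baseline variables and remove duration of IVR use. Report duration descriptively in the intervention arm.
5. Optionally, add emetogenicity derived from the recorded regimen for the CINV outcomes. It may overlap with cancer type and costs a degree of freedom with only 20 clusters.

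The cost is wording, plus coding of regimens if item 5 is taken up. No new measurement is needed and the sample size does not change. The model spends one degree of freedom on T0 and one on the stratifier if it has two levels, so the covariate set should stay that short.
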